#### Screening procedure

Potential participants undergo initial telephone interview and screening using the 13-item modified Telephone Interview for Cognitive Status (TICS-M) [32], inclusion score between 21-30/39 to exclude high cognitively functioning individuals. Health status and lifestyle behaviours are also assessed via telephone. Informants are interviewed using the Bayer-Activities of Daily Living (B-IADL) [26], Informant KATZ Index of ADL [33], and informant ratings of memory decline and concern. A subset of informants complete an in-person B-IADL form to validate the telephone version.

Participants provide signed informed consent prior to completing a series of in-person screening assessments. A flow of assessment procedures is presented in Figure 2. A structured clinical interview including psychiatric screening is completed by a neuropsychologist, and CDR score is calculated prior to physician and physical screening. If eligible after physician screening, the remainder of the baseline physical performance testing is completed, followed by baseline cognitive tests and MRI scan. If following screening a participant was excluded for low vitamin D, acute illness, or abnormal stress test or raised blood pressure, he or she may enter the study following appropriate treatment and medical review. Participants are randomised at the completion of all baseline assessments.

**Figure 2 F2:**
[figure not shown]
**SMART assessment schedule**.

### Randomisation, concealment, and allocation

A concealed, computer-generated sequence of randomly permuted blocks (block size = 8), stratified by gender and age, is generated by a statistician not otherwise involved in the study (http://www.randomization.com, created by [name], Tufts University). Randomization occurs at the completion of the entire baseline assessment. Where randomization occurs in person, assignments will be placed in sealed opaque envelopes and delivered to subjects by the recruitment officer with subjects designated to 6 months of cognitive training, progressive resistance training, combined cognitive and progressive resistance training, or stretching and video-quiz control group in a 1:1:1:1 ratio. Flow of subjects through the study to date is presented in Figure 3.

**Figure 3 F3:**
[figure not shown]
**Participant flow through SMART to date**.

### Stratification

Stratification by gender and age group (55-74; 75+) is carried out, in anticipation of the greater prevalence of women in the targeted cohort, and potential age effects on adaptation to training.

### Blinding

Subjects are informed that they will be randomly assigned to one of four treatment groups by the recruitment officer, and will be blinded to the investigators' hypothesis as to which is the preferred intervention arm. All groups will have an equal volume and frequency of contact with trainers over the 18 months of the study. All primary and secondary outcomes will be obtained and analyzed by blinded assessors on different days to the training programs.

### Interventions

All participants complete two group training sessions per week (total 26 weeks), under the supervision of trainers. Each session lasts 90 minutes and comprises approximately 45 minutes PRT or sham physical exercise (sham physical) and 45 minutes CT or sham cognitive exercise (sham CT). In order to take advantage of the enhanced attention and learning exhibited after an acute bout of exercise in both animal and human studies [34], but not enhance adaptation to sham cognitive training, PRT will proceed CT, and will follow sham CT.

Within each small group (maximum 10) participants follow the program tailored to their individual functioning level, with constant oversight by trainers. Make-up sessions are allowed for participants who miss CT and PRT sessions to achieve as close to 52 (26 × 2) sessions as possible within the 26 week intervention period. Each training group will have 1-2 trainers present at the session. The background of the trainers is in exercise physiology or physiotherapy, and the specific techniques of CT and PRT to be administered are learned from the investigators of this study ([name]).

Throughout the 18- month trial participants are provided with log books to document their social and recreational activities per day and are called weekly for telephone administration of a health status checklist. At the completion of the 6- month intervention participants are not given ongoing access to the training or advice as to what to do. Following assessments at 6 and 18 months participants receive a token reward (movie tickets or store voucher) for their participation.

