#### Sample size estimates

Sample size estimates (alpha 0.05, beta 0.20) are based on planned comparisons for the main effects of PRT and CT, as well as the effect of combined training vs. either intervention in isolation on our primary outcome: global cognitive function as assessed by ADAS-Cog. The assumptions are as follows: our meta-analyses [30] and review of published RCTs in older adults [15] reveal Effect Sizes (ES) for a range of cognitive outcomes of approximately 0.60 for cognitive training, 0.59 for aerobic/resistance training, and 0.53 for resistance training, compared to 0.15 for control groups. However, as we are enrolling a cohort with early cognitive impairment, we anticipate a decline of approximately this magnitude (ES = 0.15) over 12 months in our sample, so that the sham control condition would merely offset that decline (ES = 0.0). Thus, we have conservatively powered the study to show an ES of 0.53 for the main effects of both CT and PRT vs. control (n rounded up to 30/group × 4 = 120 required for 4-cell factorial design).

The only two published studies of *combined mental and physical training *[12,16] showed average ES = 0.94 for combined training compared to mental training alone and ES = 1.27 for combined training compared to exercise training alone. Therefore, we have ample power (99.7%) to find a difference of this magnitude between our combined training (n = 30) and isolated training groups (n = 30). Reported dropout from drug trials in MCI is 28% [31] however our experience in fully supervised training of older adults with frailty/chronic disease dropout averages 10-15% over 12 months. Therefore, we will inflate sample size needs for approximately10% drop out rate to account for anticipated attrition (n = 132), and we will recalculate these sample size needs in interim analysis after the first 50 participants have completed 6 months intervention and revise ES and sample size needs if required.

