#### Sham Cognitive and Sham Physical Exercise Control Group

In this group, subjects will receive versions of cognitive and physical exercise that are considered to be ineffective with regards to the cognitive, neurological and physical outcomes of this trial. The total session length will be 90 minutes, and all training will be supervised in groups of up to 10.

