### Statistical Analysis

We will use an intention to treat (ITT) analytic strategy as our primary analytic treatment of the data. However, we acknowledge the potential bias of any method of imputation [last observation carried forward (LOCF), mean of group, expectation maximization algorithm (EM)] or restriction to observed cases (complete case analysis). Therefore, we will make all attempts to retrieve data from dropouts by obtaining final measures regardless of intervention participation or compliance, and will use the EM method for data missing at random. In addition, we will compare characteristics of dropouts to completers and perform secondary sensitivity analyses (completers, and per-protocol analyses) to examine potential for dropouts and imputation to bias the results.

Mixed modelling of 6- and 18-month outcomes, adjusted for baseline values and any potential confounders identified will be constructed to test our primary and secondary hypotheses. We will test for main effects of CT and PRT, as well as for the interaction term (CT × PRT) to identify isolated and combined training arm significance and effects sizes. Relationships of interest and risk factors for changes in cognitive function and other secondary outcomes will be analysed with simple and multivariate linear and logistic regression models as appropriate. Weighted mean differences, 95% Confidence Intervals and Effect Sizes will be calculated for all outcomes, and clinical meaningfulness will be assessed in light of available data on the expected annual rates of change in this cohort for all known primary and secondary outcome variables.

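### Training is delivered in supervised groups in every arm, but the sample size allows nothing for clustering and the described model names no training-group or trainer term

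*Protocol article*

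**What the plan says.** Randomisation, concealment, and allocation describes individual randomisation, 1:1:1:1, to four arms. Delivery is in groups. Under Interventions, "All participants complete two group training sessions per week (total 26 weeks), under the supervision of trainers". The same section caps a group at 10 and puts one or two trainers at each session. For the double-sham arm, "all training will be supervised in groups of up to 10".

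Sample size estimates gives these inputs: "Sample size estimates (alpha 0.05, beta 0.20) are based on planned comparisons for the main effects of PRT and CT", and "we have conservatively powered the study to show an ES of 0.53 for the main effects of both CT and PRT vs. control". The result is "n rounded up to 30/group × 4 = 120 required for 4-cell factorial design", raised to 132 for dropout. No ICC, design effect or group size enters.

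Statistical Analysis plans "Mixed modelling of 6- and 18-month outcomes, adjusted for baseline values and any potential confounders identified", with main effects of CT and PRT and their interaction. It lists no random effects. The Covariates section includes neither training group nor trainer.

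The article does not say whether a training group holds one arm or several, whether membership is fixed, or whether trainers work across arms.

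**The concern.** People who train together twice a week for half a year share a trainer, company and calendar period. Their outcomes may therefore be more alike than those of people in different groups. When such groups sit within arms, group-to-group variation adds to the variance of the arm comparison. A formula or model that leaves it out then overstates the information in 120 people. The tests of the CT and PRT main effects would reject too often, and a good group or trainer could pass for a benefit of the training type. The main effects matter most here because the sample size has little reserve for them.

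**Working it through.** **Inputs.** From Sample size estimates: alpha 0.05 (taken as two-sided, which fits), power 0.80, effect size 0.53, and 30 per cell, so 60 v 60 for each main effect. From Interventions: groups of up to 10. The ICC is not in the document; I assume 0 to 0.05.

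**Reproducing the plan's figure.** n per factor level = 2 × ((1.960 + 0.842) / 0.53)² = 55.9, so 56, or 28 per cell. The t-test version needs 57 per level, or 29 per cell. Rounding up to 30 gives 120. Both formulas assume independent participants.

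**Reserve.** At 60 v 60 the noncentrality is 0.53 × √(60/2) = 2.903. Power is 82.1% by the noncentral t (118 df) and 82.7% by the normal approximation. Power drops below 80% once the design effect passes about 1.06 (t) or 1.07 (normal). By the normal figure that is an ICC of about 0.07/9 = 0.008 in groups of 10, or 0.07/4 = 0.018 in groups of 5.

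**Plausible group size.** Recruitment runs from October 2008 to December 2011, 39 months. Assuming even accrual, 132/39 = 3.4 join per month. With six months of training, 3.4 × 6 ≈ 20 are in training at once, about 5 per arm. If groups are arm-specific, 5 is a more typical size than 10.

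**Effect of clustering within arms.** Design effect DE = 1 + (m − 1) × ICC. Power is from the noncentral t with noncentrality 2.903/√DE. True alpha of a test that ignores groups = 2 × (1 − Φ(1.96/√DE)).

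| Group size m | ICC | DE | SE ratio √DE | Power | True alpha |
|---|---|---|---|---|---|
| any | 0 | 1.00 | 1.00 | 82% | 5.0% |
| 5 | 0.01 | 1.04 | 1.02 | 81% | 5.5% |
| 5 | 0.02 | 1.08 | 1.04 | 79% | 5.9% |
| 5 | 0.05 | 1.20 | 1.10 | 75% | 7.4% |
| 10 | 0.05 | 1.45 | 1.20 | 67% | 10.4% |

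The last row is an upper bound, not a typical case. The powers keep 118 degrees of freedom. As a conservative bound, 120/5 = 24 groups and 24 − 4 = 20 df give about 77% instead of 81% at ICC 0.01.

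**Combined v single training, 30 v 30.** The plan cites "average ES = 0.94 for combined training compared to mental training alone and ES = 1.27 for combined training compared to exercise training alone" and says "we have ample power (99.7%) to find a difference of this magnitude". By the normal approximation, Φ(ES × √(15/DE) − 1.96), power at 1.27 is 99.8% under independence and 98.3% at DE 1.45. At 0.94 it is 95.4% and 85.6%. On the plan's own effect sizes this comparison is not where the problem lies.

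**The case against.** A reader might infer that the planned model treats participants as independent and that its standard errors will therefore be too small. The document does not support this. Statistical Analysis says the modelling is mixed and lists no random effects of any kind. This is a condensed article, and a SAP that is not shown may add a group term. Silence here is not exclusion.

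A reader might also infer stable single-arm groups with the same trainers throughout. The article says only how many trainers are present at a session. Make-up sessions may blur membership, and individually tailored programmes and separate computer workstations may keep the ICC low. If groups mix arms, the simple design effect does not apply. Some text leans towards arm-specific groups: session order depends on arm, and PRT has its own staffing ratio. That does not settle the matter.

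Two further objections stand in part. The plan promises 80%, not 82%, and at ICC 0.01 in groups of 5 the computed power is still 80.6% on 118 df, so power is not overstated in every scenario. And if each arm ran as one rolling session, group would coincide with arm and a random intercept could not be separated from treatment. The second objection limits how group may be defined; it does not remove the need to consider it.

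None of this affects the sample size calculation, which is written out and allows nothing for clustering.

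**Conclusion.** The point holds as a gap in planning with a conditional consequence. It is not a demonstrated error in the model. Group delivery in every arm is certain, and the reproduction shows that the sample size assumes independence with room for a design effect of only about 1.06 to 1.07. The consequence needs a positive ICC, groups largely within arms, and a final model without a group term. Under those conditions, with groups of 5 and ICCs of 0.01 to 0.05, main-effect power is about 1 to 7 points below the 82% under independence, true alpha is about 5.5% to 7.4%, and correct intervals are about 2% to 10% wider. The 67% power and 10.4% alpha for groups of 10 at ICC 0.05 mark the upper end of the range considered and fit planned accrual poorly. With an ICC of 0 there is no loss. It is a worthwhile, inexpensive improvement.

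**What to change.** 1. State whether training groups are arm-specific and whether trainers work across arms.
2. Record each participant's main session group or cohort period, and main trainer. With make-up sessions, use the group attended most.
3. Add a random intercept for training group to the primary mixed model, with a small-sample degrees-of-freedom correction such as Kenward-Roger. Define group by session slot and calendar period so that it does not coincide with arm. If there are too few groups to estimate the term, prespecify it as a sensitivity analysis instead. Report the estimated ICC either way.
4. Restate the main-effect power in Sample size estimates as a range over plausible ICCs. The recalculation already planned after the first 50 completers is a natural occasion.

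The cost is two variables taken from attendance records and one model term. Intervals become slightly wider, and stated power falls by about 1 to 7 points in the plausible range, somewhat more once the degrees of freedom reflect the number of groups. With few groups the ICC will be imprecise and should be reported with its interval. No extra participants and no change to training or visits are needed.

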#### Cognitive Training Intervention (+ Sham physical)

Cognitive training (CT) intervention involves computer-based multimodal and multi-domain exercises targeting memory, executive function, attention and speed of information processing. The training uses the COGPACK program [35], developed for neuro-rehabilitation and used in a previous research trial with MCI [36]. A total set of 14 exercises have been selected including six tasks of visual and verbal explicit memory ('Reading', 'Memory for names', 'Memory for shopping list', 'Memory for forms', 'Memory for route', 'Memory for traffic signs'), four tasks of executive function ('Anagrams', 'Sequence', 'Logic blocks', 'Logic') and four attention and speed tasks ('Reaction', 'Connect' UFOs' and 'Search'). The training schedule was pre programmed with 4 exercises being administered at each 45-minute training session. Training sessions are completed in a group setting with up to 10 computer work stations, and simple touch screens to avoid training difficulties in the computer-naïve.

#### Progressive Resistance Training (+ Sham cognitive)

Progressive resistance training (PRT) is supervised by experienced research assistants (exercise physiologists and physiotherapists) in a medically-supervised clinic (University of Sydney Health Sciences) at a ratio of 1 trainer for 4-5 subjects. The specifics of the high intensity training intervention are summarised in Table 2. Participants are progressed continuously throughout the 6-month intervention, guided by daily ratings of perceived exertion (15-18 on the Borg Scale [37] and 1RM's every 3 weeks to maintain intensity at 3% from 80 to 92% of current maximum capacity). Maximization of potential cognitive- enhancing effects of the PRT is supported by introduction of novel exercise after every 8 sessions and encouraging visualisation, counting out loud, and imagery of the muscle repetitions contracting during rest intervals.

**Table 2 T2:** Progressive Resistance Training Methodology

	Exercise	Equipment	Frequency	Volume	Intensity progression
Routine	Seated Chest press	Digital K400 Keiser pneumatic resistance machines (Keiser Sports health Equipments, Inc. Fresno, CA)	2 sessions/wk	3 sets of 8 per session	80% of the most recently measured 1RM progressed each session s tolerated using RPE* 15-18 (approximately 3% per session)
	Seated leg press				
	Seated row				
	Standing hip abduction				
	Knee extension				

Novel	Lateral raise	Free weights (dumbbells)	4 weeks or 8 sessions	3 sets of 8 per session	15-18 RPE
	Hip flexion	Keiser			
	Calf raise	Keiser			
	Hip extension	Keiser			
	Bicep curls	Free weights (dumbbells)			

*RPE Ratings of perceived Exertion Borg Scale [37]

#### Combined CT and PRT

This group will receive both the cognitive training intervention and progressive resistance training intervention, delivered on the same day within 90-minute sessions.

#### Sham Cognitive and Sham Physical Exercise Control Group

In this group, subjects will receive versions of cognitive and physical exercise that are considered to be ineffective with regards to the cognitive, neurological and physical outcomes of this trial. The total session length will be 90 minutes, and all training will be supervised in groups of up to 10.

#### Sham Cognitive

Sham CT involves video exposure to a variety of general interest documentary topics, such as travel, culture, and history (National Geographic), and tailored to suit the audience and their expectation of training, are followed by a set of simple questions regarding the presented material. Previous CT trials used this type of active control condition [38] with minimal impact on cognitive outcomes.

#### Sham Physical

Sham physical exercise (Sham physical) will include stretching and seated calisthenics designed so as not to notably increase heart rate or aerobic capacity, improve balance, or enhance strength. No use of equipment and no progression will be included. This regime allows for maintenance of the double blind design as it is similar to what older adults anticipate receiving in senior group exercise classes. Furthermore, in contrast to aerobic activity, such a regimen has been shown recently to have no effects on brain volume in older adults [18].

### Adverse Events

Monitoring of adverse events will be achieved by weekly questionnaire/interview- and proxy information will be obtained whenever necessary to minimize missing data. Adverse events will include any exacerbation of underlying disease, or new onset musculoskeletal, cardiovascular, or metabolic abnormality attributed directly to study protocols.

Specific adverse events that will be routinely monitored include: falls, cardiac events during physical testing and exercise training (angina, arrhythmias, blood pressure excursions, clinically significant ECG changes); fatigue and muscle soreness or musculoskeletal injury after resistance or sham physical training; anxiety during MRI scan or cognitive or sham cognitive training; pain or injury related to movement of ferromagnetic devices, implants, shrapnel during MRI scan; and pain, bruising, or infection at the venipuncture site. In addition, subjects will be asked to report all changes in medication, health care professional visits, new diagnoses, acute illnesses, or any new symptoms.

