## Results

We originally estimated the need for a sample size 10% larger than our expected effect size required (n = 132). With our retention rate of >90% to date our recruitment target remains appropriate 120/.90 = 133. Thus, we have recruited 80/133, 60% of our planned cohort to date. Compliance with training sessions to date has been high for all groups with median compliance ranging from 78.44% for sham physical/CT to 100% for PRT/CT. Furthermore there has been one adverse event reported thus far (one rotator cuff injury managed conservatively) in PRT group, and no adverse events during assessments, CT, or sham interventions.

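### The general adverse event definition makes attribution to the study a condition for counting new-onset abnormalities, at odds with the unconditional monitoring list and weekly reporting beside it

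*Protocol article*

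**What the plan says.** The Adverse Events section of the protocol article contains three layers.

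- **General definition:** adverse events will include an exacerbation of existing disease, "or new onset musculoskeletal, cardiovascular, or metabolic abnormality attributed directly to study protocols". The closing qualifier certainly governs new-onset abnormalities. Grammatically it may also govern exacerbations.
- **Specific list, with no attribution condition:** "Specific adverse events that will be routinely monitored include: falls, cardiac events during physical testing and exercise training", and also "fatigue and muscle soreness or musculoskeletal injury after resistance or sham physical training", together with items for scanning, cognitive sessions and blood sampling.
- **Open reporting:** "subjects will be asked to report all changes in medication, health care professional visits, new diagnoses, acute illnesses, or any new symptoms". Collection is regular: "Monitoring of adverse events will be achieved by weekly questionnaire/interview". The Interventions section has weekly telephone checklists for all participants throughout the 18 months.

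On blinding, the Blinding section says: "All primary and secondary outcomes will be obtained and analyzed by blinded assessors on different days to the training programs". Adverse events appear in none of the outcome tables (Tables 3 to 7).

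The Results section gives a progress remark: "there has been one adverse event reported thus far (one rotator cuff injury managed conservatively) in PRT group", with none noted for assessments, cognitive training or sham, at a point when 80 people had been recruited.

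**The concern.** Randomisation protects a comparison of harms only if events are counted by the same rule in each arm, whatever their presumed cause. Under the general definition, a new-onset abnormality counts once somebody has linked it to the study. That link is a judgement, and the natural basis for it is what the participant has been doing: lifting heavy loads or stretching in a chair. Nothing stated makes the judgement blind to arm. If it depends on arm, the difference between arms reflects the judgement as well as the treatment.

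The section also leaves two rules for what counts side by side. A new diagnosis reported on a weekly call is collected in every arm, yet it falls outside the general definition unless it is attributed. At stake is how well the trial can describe the safety of high-intensity PRT in older people with chronic disease.

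**Working it through.** The plan states no adverse event rate, margin or power, so there is no figure to reproduce. The check compares the texts and then shows by arithmetic what an attribution condition can do.

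**1. Which events depend on the general definition?** The list covers falls without restriction. Its cardiac item is confined to testing and training, and its musculoskeletal item to the aftermath of a physical session. Three kinds of event are left to the general definition:
- cardiovascular events away from the sessions;
- new metabolic abnormalities;
- musculoskeletal problems that do not follow a session.

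For these, attribution decides whether they count. Training ends at 6 months and follow-up runs to 18 months, so for two thirds of the period (12 of 18 months) there is no current training to attribute an event to.

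**2. Two readings of the qualifier.** If it governs only new-onset abnormalities, an event put down to existing disease still counts as an exacerbation. If it governs both, that event is lost unless it is also attributed to the study. The text does not settle which is meant.

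**3. Effect of an attribution condition.** Planned size: 30 per group in four groups, so 60 PRT against 60 sham physical at the factorial margin. Counted risk = true risk × probability of attribution. The last column is the chance of a nominal two-sided 5% difference, Φ[(|d| − 1.96·SE₀)/SE₁], where d is the difference in counted risks, SE₀ uses the pooled risk and SE₁ the two separate risks. All true risks and attribution probabilities are assumptions.

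| True risk, PRT / sham | Attributed, PRT / sham | Counted, PRT / sham | Difference (points) | Ratio | Chance of p<0.05 |
|---|---|---|---|---|---|
| 30% / 15% | all / all | 30% / 15% | 15 | 2 | 0.50 |
| 30% / 15% | 50% / 50% | 15% / 7.5% | 7.5 | 2 | 0.25 |
| 30% / 15% | 20% / 20% | 6% / 3% | 3 | 2 | 0.12 |
| 30% / 15% | 50% / 10% | 15% / 1.5% | 13.5 | 10 | 0.77 |
| 30% / 15% | 25% / 50% | 7.5% / 7.5% | 0 | 1 | no difference left |
| 20% / 20% | 50% / 10% | 10% / 2% | 8 | 5 | 0.45 |

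Equal attribution keeps the ratio but shrinks the difference and the information. Unequal attribution can exaggerate a difference, erase it, or create one where none exists. Counts within an arm can only fall; the bias between arms has no fixed sign. The normal approximation is rough where counts are small (1.5% of 60 is 0.9 people).

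**4. What the reported tally can show.** One in 80 is 1.25% (exact 95% interval 0.03% to 6.8%). If the 80 split evenly, 40 had sham physical training, and zero in 40 has an upper limit of 1 − 0.025^(1/40) = 8.8%. These limits reflect small numbers and would be as wide without any attribution condition.

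The probability of at most one affected person depends on an assumed risk and on how many had meaningful exposure:
- assumed risk 5%: 0.086 with 80 exposed, 0.40 with 40;
- assumed risk 10%: 0.002 with 80 exposed, 0.08 with 40.

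The documents supply neither input, so the tally cannot be used to infer a filter.

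**The case against.** The best defence is that the section as a whole is broad. The definition says what adverse events will include, which is not stated to be exhaustive. The specific list is unconditional, covers falls, cardiac events in training, and injury after PRT or sham in identical terms, and takes in the main foreseeable harms of lifting. Everything else is reported weekly in every arm, so an unfiltered comparison can be made from the planned data. This stands, and it rules out several stronger readings:

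- A reader might infer that new-onset events count only when attributed. The unconditional list contradicts this.
- A reader might infer that unattributed reports are discarded. The article does not say so; it leaves their status unclear.
- A reader might infer that trainers who know the arm make the attribution. The article names nobody. Who judges, and by what criteria, is detail that an article may leave to the full protocol, so its absence is not the point.
- A reader might infer that a planned test of harms is biased, or that the trial can support no safety statement. The objectives and hypotheses include no safety hypothesis, the Statistical Analysis section states no test of adverse events, and the unfiltered reports remain available.
- A reader might infer that one event among 80 shows the filter at work. It does not, as shown above.

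What the defence leaves untouched is the stated condition itself. It is in the definition, the list beside it does not carry it, and the two give different counts for the same participant.

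**Conclusion.** The point holds as a flaw in the stated definition. It conflicts with the unconditional monitoring and open reporting in the same section. A tabulation that followed it would miss events and could move the PRT versus sham contrast either way. Its size cannot be derived from the documents. The illustration, in which a true ratio of 2 becomes 10 or 1, rests wholly on assumed risks and attribution probabilities and shows what is possible, not what is expected.

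The conclusion assumes that the definition governs at least some of the reported counts, and that attribution is not made blind to arm, since the article promises blinding only for primary and secondary outcomes. It is worth correcting because the information needed is already being collected.

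**What to change.** In the Adverse Events section:

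- Delete the attribution condition from the definition, which also removes the doubt over whether it covers exacerbations.
- Count all new or worsened conditions, injuries and falls reported on the weekly checklist over the 18 months, whatever their presumed cause.
- Tabulate them by randomised arm, and as PRT versus sham physical at the factorial margin.
- Record relatedness as a separate descriptor, judged blind to arm where possible.
- Let a health-care visit prompt a query about a new or worsened condition. The visit is not itself an event, because routine check-ups would then swell the count.

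The cost is a change of wording and some coding of reports already collected. The downside is a longer event table that includes background illness; the relatedness field lets a reader separate the two.
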